## Abstract

**Background:**

Acute promyelocytic leukemia (APL) is a highly curable disease when treated with all-trans retinoid acid (ATRA) and arsenic trioxide (ATO). The combination of ATO and ATRA has become the standard therapeutic protocol for induction therapy in non-high-risk APL. An oral arsenic realgar-indigo naturalis formula (RIF) has also showed high efficacy and it has a more convenient route of administration than the standard intravenous regimen. Unlike in previous trials, the arsenical agent was used simultaneously with ATRA during post-remission therapy in this trial.

**Methods:**

This study was designed as a multicenter, randomized controlled trial. The trial has a non-inferiority design with superiority being explored if non-inferiority is identified. All patients receive ATRA-ATO during the induction therapy. After achieving hematologic complete remission (HCR), patients were randomly assigned (1:1) to receive treatment with ATRA-RIF (experimental group) or ATRA-ATO (control group) as the consolidation therapy. During the consolidation therapy, the two groups receive ATRA plus RIF or intravenous ATO 2 weeks on and 2 to ~ 4 weeks off until molecular complete remission (MCR), then ATRA and oral RIF 2 weeks on and 2 to ~ 4 weeks off giving a total of six courses.

**Discussion:**

This trial aims to compare the efficacy of ATRA-ATO versus ATRA-RIF in non-high-risk patients with APL, to demonstrate that oral RIF application reduces the total hospitalization days and medical costs. The simple schedule was studied in this trial.

**Trial registration:**

ClinicalTrials.gov, NCT02899169. Registered on 14 September 2016.

## Background

Acute promyelocytic leukemia (APL) is characterized by a chromosomal translocation of t (15; 17) (q22; q21), involving the retinoic acid receptor alpha (RARα) and promyelocytic leukemia (PML) [1]. Before the use of all-trans retinoid acid (ATRA) APL was a highly fatal disease because of potentially severe coagulopathy [2]. Recent clinical trials have demonstrated that high complete remission (CR) rates and disease-free survival (DFS) can be achieved using a combination of ATRA and arsenic trioxide (ATO) as a first-line treatment for newly diagnosed APL [3–6].

Moreover, the GIMEMA group demonstrated broadly better quality of life (QoL) outcomes post-induction, favoring treatment with intravenous ATO compared to standard chemotherapy [7]. ATRA combined with oral realgar-indigo naturalis formula (RIF) has been shown to reduce the medical costs and length of hospital stay during induction and remission therapy compared with ATO plus ATRA in patients with APL [8]. Based on these clinical trials, compared with intravenous ATO, oral RIF may achieve comparable remission and survival outcomes at a lower cost and with a shorter hospital stay when used as the first-line treatment in APL.

Different arsenical agents were used in previous trials, such as oral RIF, tetra-arsenic tetra-sulfide [9] or intravenous ATO, and ATO was also used in different doses and schedules. For example, ATO was used at 0.15 mg/kg body weight/day for 5 days/week for 4 weeks every 8 weeks in study APL0406 [4], but in study AML17 [10], ATO was used at 0.25 mg/kg body weight/day twice a week in post-remission therapy. In this randomized, controlled trial, a new protocol was designed with the aim to simplify treatment and to further improve the curative effect.

## Methods

### Study hypothesis

The hypothesis is that ATRA-RIF is not inferior to ATO-ATRA in treating non-high-risk APL. Application of oral RIF may reduce the total hospitalization days and medical costs. The simultaneous application of oral RIF and ATRA is more convenient for patients and improves the efficacy.

### Eligibility criteria

Patients will be enrolled from the following hospitals: The First Affiliated Hospital of Xi’an Jiaotong University and Tang-Du Fourth Military Medical University of Chinese PLA. All study participants will provide signed written informed consent before participation. All participants will go through a standardized interview process and receive more information about the study and the treatments. The purpose, procedures, potential risks and benefits of the study will also be explained thoroughly to the participants. The participants will be able to withdraw from the study at any time without consequence.

### Inclusion criteria

Participants meeting the following criteria will be included:
Age 14–75 yearsNewly diagnosed APL with t (15; 17) (q22; q12)Pre-treatment peripheral blood white blood cell (WBC) count < 10 × 10^9^/LAble to complete the entire treatment processSigned written informed consent provided by the patient or their family

### Exclusion criteria

Participants meeting one or more of the following criteria will be excluded:
Allergy to the drug ingredient or the supplementary material, or having an allergic constitution Cardiac insufficiency (cardiac contraindications to intensive chemotherapy (left-ventricular ejection fraction (L-VEF) < 50%)).Inadequate renal reserve (defined as total creatinine > 3 times the institutional upper limit of the normal range)Significant arrhythmias, electrocardiogram (EKG) abnormalities (congenital long QT syndrome; history or presence of significant ventricular or atrial tachyarrhythmia; clinically significant resting bradycardia (< 50 beats per minute); QTc > 450 ms on screening EKG; right bundle branch block plus left anterior hemiblock, bifascicular block)Combined with other malignant tumorsPregnant and lactating womenParticipants in other drug trials in the last 3 monthsSuffering from mental illness or other circumstances which render them unable to complete the treatment plan

### Sample size calculation

On the basis of the previous studies [4, 9, 11] assuming 97% DFS in the control (ATO) group, and conservatively assuming 99% DFS in the experimental (RIF) group, a noninferiority margin of − 5%, follow up of 2 years, 5% type I error (one-sided), 90% power, we used PASS 11 to calculate a required sample size of 53 evaluable patients per group to draw a conclusion of non-inferiority. Allowing for a withdrawal rate of 10%, 59 patients per group will be required. Therefore, we plan to enroll 118 patients into two groups (1:1). We plan a final analysis only, with no interim analysis. The design of this trial is a non-inferiority trial with superiority being explored if non-inferiority is identified.

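### The sample size calls 99% DFS on RIF against 97% on ATO conservative, but this is the favourable direction for non-inferiority, and the 90% power depends on that 2-point advantage

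*Protocol article*

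**What the plan says.** The Sample size calculation lists its inputs as "assuming 97% DFS in the control (ATO) group", "conservatively assuming 99% DFS in the experimental (RIF) group", "a noninferiority margin of − 5" percent, "follow up of 2 years", "5% type I error (one-sided") and 90% power. It then reports: "we used PASS 11 to calculate a required sample size of 53 evaluable patients per group". A 10% withdrawal allowance brings this to 59 per group, 118 in total. The rates are attributed to earlier studies, but no figures from those studies are given and the PASS procedure is not named.

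Elsewhere, the Study hypothesis reads: "The hypothesis is that ATRA-RIF is not inferior to ATO-ATRA in treating non-high-risk APL". The Background, summarising earlier trials, says that "oral RIF may achieve comparable remission and survival outcomes" at lower cost and with less time in hospital.

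**The concern.** In a superiority trial, a cautious planner assumes a small effect. The matching caution in a non-inferiority trial is to assume no advantage, or a slight disadvantage, for the new treatment. Assuming that RIF is 2 points better does the reverse and makes the trial smaller.

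The article gives no reason for a DFS advantage of RIF over ATO. The simultaneous use of ATRA and the arsenical is presented as a gain in efficacy, but the Consolidation therapy section gives ATRA together with the arsenical in both arms. The Discussion suggests that intravenous ATO may bring faster molecular remission. The advantages argued for RIF are convenience, cost and hospital days.

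A reader of the sample size paragraph would conclude that the trial has 90% power under a cautious assumption. If RIF is only as good as ATO at 97%, the chance of showing non-inferiority is far lower.

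**Working it through.** **Inputs (Sample size calculation).** Control DFS pc = 0.97; experimental DFS pe = 0.99; margin 0.05, read as an absolute difference; one-sided α = 0.05 (z = 1.645); power 0.90 (z = 1.282); (1.645 + 1.282)² = 8.564.

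**Reproducing 53.**

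- *Normal formula, unpooled variance:* n = 8.564 × [pc(1 − pc) + pe(1 − pe)] / (pe − pc + 0.05)² = 8.564 × (0.0291 + 0.0099) / 0.07² = 68.2, so 69 per group. This is not 53.
- *Exact binomial enumeration of the Z test:* power is 85.7% at n = 52 and 91.9% at n = 53, so 53 is the first size to reach 90%. This reproduces the stated figure.
- *Withdrawal:* 53 / 0.9 = 58.9, so 59 per group and 118 in total, as stated.

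The normal formula also returns 53 if the margin is 6 points (8.564 × 0.039 / 0.08² = 52.2), but the article states 5. At the stated inputs, the enumerated Z test is the only method tried that gives 53. That this was the sponsor's method is an inference.

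**Direction of the assumption.** With both arms at 97%, the distance to the margin falls from 0.07 to 0.05 and the variance sum rises from 0.0390 to 0.0582. Then n = 8.564 × 0.0582 / 0.05² = 199.4, so 200 per group against 69. Exact Z-test enumeration gives 201 or more against 53. The 2-point advantage therefore cuts the requirement to about a third or less.

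**Power at 53 per group, normal formula:** Φ{(pe − pc + 0.05) / √([pc(1 − pc) + pe(1 − pe)] / 53) − 1.645}.

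- 99/97: 0.07 / 0.02713 − 1.645 = 0.936, power 82.5%
- 98/97: 0.06 / 0.03031 − 1.645 = 0.335, power 63.1%
- 97/97: 0.05 / 0.03314 − 1.645 = −0.136, power 44.6%

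**By all three methods, 53 per group, margin 5 points, nominal one-sided 5%:**

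| True DFS, RIF/ATO | Exact Z test (gives 53) | Normal formula | Exact score test (Farrington–Manning) |
|---|---|---|---|
| 99% / 97% | 91.9% | 82.5% | 74.2% |
| 98% / 97% | 75.7% | 63.1% | 53.4% |
| 97% / 97% | 58.4% | 44.6% | 37.4% |
| True type I error at 92% / 97% | 9.8% | not applicable | 4.9% |

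The Z test gains its extra power by rejecting too often at the margin, almost twice the stated 5%. The score test stays close to 5%.

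If all 59 per group were evaluable, power at 97/97 would be 54.4% (Z), 47.9% (normal) and 35.9% (score), so the withdrawal allowance does not restore it.

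**Dependence on the common rate.** If the arms are equal at a higher rate, power at 53 is higher: 73.1%, 57.7% and 45.3% at 98/98, and 90.3%, 82.7% and 61.8% at 99/99 (Z, normal, score).

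**The case against.** Several points on the other side have force.

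- *The word may have another meaning.* It could mean that 99% lies below what the cited RIF studies found. Those figures are not in the article, so this cannot be checked. It would explain the word, but it would not make the assumption conservative for sample size, because the calculation would still rest on RIF being better.
- *The hypothesis does not suppose equality.* A reader might infer that a non-inferiority hypothesis commits the sponsor to equal arms, so that 97/99 contradicts it. It does not: any true difference above −5 points is non-inferior. The Background's expectation of comparable results is hedged and does not exclude 2 points. It makes equality a natural planning case that the article should have covered, and no more than that.
- *Power under equality is not one number.* A reader might infer that it is about 45% or less. The 45% comes from the normal formula, which does not reproduce 53. The test that does reproduce it gives 58%. All of these figures also require a common rate of 97%.
- *The inflated error of the Z test is a separate defect.* This is true, but it bears on which power figure may be quoted beside a stated 5% error.
- *The assumption is disclosed.* A reader can work out the sensitivity from the stated rates. But the article labels the assumption as cautious, which tells the reader that there is no need to.

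Nothing in the article says that a failed result would be read as evidence against RIF, and that is not alleged here.

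**Conclusion.** The point holds in this form. Describing 99% on RIF against 97% on ATO as conservative is wrong as a statement about sample size: the assumption is favourable, and the article gives no reason for a 2-point advantage. The 90% power depends on it. At 53 per group and RIF truly at 97%, power is 58%, 45% or 37% by the exact Z test, the normal formula or the score test, so even the most generous method leaves about a 42% chance of failure (100 − 58) against the 10% that the reader is given. Under the planned 97/99, a test that holds about 5% has 74% power rather than 90%.

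These figures assume an absolute 5-point margin, a comparison of 2-year proportions and 53 evaluable patients per group. They do not show that RIF lacks an advantage, that the trial must fail if the arms are equal, or that the planned analysis will be the Z test.

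**What to change.** In the Sample size calculation, delete *conservatively* and put wording of this kind in its place:

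> The sample size and its stated power rest on an assumed 2-point advantage in 2-year DFS for RIF (99% against 97%). With 53 evaluable patients per group, a margin of 5 percentage points and a one-sided 5% score test (Farrington–Manning), power is 74%, 53% and 37% if true DFS on RIF is 99%, 98% and 97% and on ATO is 97%. The 90% first stated corresponds to a Z test whose true type I error is about 9.8% at 92% against 97%. Failure to show non-inferiority at this size will be reported as inconclusive, not as evidence of inferiority.

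The sponsor should confirm from its PASS output which procedure gave 53 before attributing the 90%. If it names a different test for the primary comparison, all three power figures should come from that one test, with its true error stated. If *conservatively* referred to the cited RIF results, give those results and say so.

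The cost is protocol wording and a less favourable stated power. Enrolment, endpoint and margin do not change.

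### 53 evaluable patients per group cannot give both a 5% one-sided error and 90% power; a test that holds the error near 5% has about 74% power

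*Protocol article*

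**What the plan says.** The protocol article, under Sample size calculation, gives these inputs:

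- control arm: "assuming 97% DFS in the control (ATO) group"
- experimental arm: "conservatively assuming 99% DFS in the experimental (RIF) group"
- margin, in percentage points: "a noninferiority margin of − 5"
- error: "5% type I error (one-sided"
- power of 90%, with "follow up of 2 years"

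The result is stated as: "we used PASS 11 to calculate a required sample size of 53 evaluable patients per group to draw a conclusion of non-inferiority". It then adds: "Allowing for a withdrawal rate of 10%, 59 patients per group will be required". Total enrolment is 118, allocated 1:1.

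The Outcome measures section makes the 2-year DFS rate the primary outcome, so a comparison of two proportions is the natural reading. Neither the sample size section nor the Statistical analysis section names the non-inferiority test. The latter only exempts it from the two-sided 0.05 rule.

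**The concern.** With these inputs the textbook formula gives a clearly larger sample than 53. Expected failures are very few: 53 × 0.03 = 1.6 in the control group and 53 × 0.01 = 0.5 in the experimental group. With so few events, a z-test run at a nominal 5% can have a very different true error, so power computed for it may be bought with extra false-positive risk.

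This is the trial's main claim, and superiority is to be explored only if non-inferiority is shown. If the analysis uses the z-test, a positive result carries a risk of wrongly accepting an arm that is 5 points worse well above the declared 5%. If it uses a test that holds 5%, a failure to show non-inferiority will be read as coming from a 90%-power trial when the power was much lower.

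**Working it through.** **Inputs** (all from Sample size calculation): control DFS 0.97, experimental DFS 0.99, margin 0.05, one-sided α = 0.05 (z = 1.645), power 0.90 (z = 1.2816). The distance from the margin under the planning assumption is 0.02 + 0.05 = 0.07.

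**1. Reproducing 53.** I enumerated all outcome tables for two binomial groups and applied the uncorrected unpooled z-test at nominal one-sided 5%, counting a table with no failures in either group as a success. Power is 0.857 at n = 52 and 0.919 at n = 53, so 53 is the first size above 90%. The pooled version gives the same result.

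The jump comes from one table, with no control failures and one experimental failure:

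- n = 52: z = (0.05 − 1/52) / √[(1/52)(51/52)/52] = 1.616, below 1.645
- n = 53: z = (0.05 − 1/53) / √[(1/53)(52/53)/53] = 1.666, above 1.645

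If zero-failure tables do not count as success, power at 53 is 0.802. The withdrawal step is correct: 53 / 0.9 = 58.9, so 59.

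**2. Standard formula.**

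n = (1.645 + 1.2816)² × (0.97 × 0.03 + 0.99 × 0.01) / 0.07² = 8.564 × 0.039 / 0.0049 = 68.2, so 69 per group.

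Power at n is Φ(0.07 / √(0.039/n) − 1.645), which is 0.825 at 53 and 0.859 at 59.

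**3. True error of the z-test.** The same enumeration on the margin (experimental DFS 5 points below control) gives:

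| Control DFS | n = 53 | n = 59 |
|---|---|---|
| 95% | 7.6% | 6.0% |
| 97% (planning value) | 9.8% | 7.5% |
| 98% | 12.2% | 9.2% |
| 99% | 16.9% | 12.8% |

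**4. A test that holds the error.** The Farrington-Manning score test, by exact enumeration:

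| | n = 53 | n = 59 |
|---|---|---|
| Error at 97% vs 92% | 4.9% | 4.2% |
| Power at 97% vs 99% | 74.2% | 73.8% |

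Power does not rise from 53 to 59 because the outcomes are discrete: for 0 to 4 control failures, the number of experimental failures allowed is the same at both sizes. Exact power first reaches 90% at n = 87 (88 for Miettinen-Nurminen). At 69, the formula's answer, it is 84.8%.

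**5. Could any other test rescue 53?** By the Neyman-Pearson lemma, the most powerful test with a true 5% error at 97% vs 92% has 80.2% power against 97% vs 99% at n = 53. Requiring the error to hold at control DFS of 99% as well lowers the bound to 73.9%. At n = 59 the bound at 97% vs 92% is 88.7%.

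**The case against.** The strongest reply is that nothing was miscalculated. The number 53 is what the software would return for an uncorrected z-test, and sample size statements often give a nominal level. Read that way, 53, 5% and 90% are all true of that test. It is right that 53 is not an arithmetic slip. However, the protocol states a 5% type I error as a property of the design, and the bound in step 5 shows that no test with that property reaches 90% at 53. The choice of test in an analysis plan that is not shown cannot change this.

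Three further points stand as limits on the finding:

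- The route to 53 is inferred from an exact match. The test is not named, and the match needs zero-failure tables to count as success. The normal formula at one-sided α = 0.10 also gives 53 (52.3 rounded up).
- The inflated error arises only if the z-test is used in the analysis. If all 59 per group are analysed under intention to treat, it is 7.5%, not 9.8%. The 12% to 17% figures at n = 53 need a control DFS of 98% to 99%, above the planning value.
- The normal formula is unreliable with so few events, so 69 and 82.5% are not the figures to rely on. The exact score-test result is.

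**Conclusion.** The concern holds. Under the protocol's own assumptions, 53 evaluable patients per group, a true one-sided 5% error and 90% power are incompatible. Either the error is about 10% at the planning control rate (7.5% if all 59 per group are evaluable), with power just over 90%, or the error is held near 5% and power is about 74% at either size. The shortfall against the stated 90% is then about 16 points, far beyond rounding between methods.

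This rests on reading the primary comparison as a difference between two binomial proportions at 2 years with complete follow-up of evaluable patients, and on the planning rates of 97% and 99%. The score test is itself only approximately 5%: at n = 53 its error is 5.1% at control DFS of 99% and at most 6.6%, reached at 100%.

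**What to change.** Keep 118 patients and rewrite the Sample size calculation section to:

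- name the non-inferiority test assumed, a score test (Farrington-Manning or Miettinen-Nurminen) on the difference in 2-year DFS at one-sided 5%;
- withdraw the 90% claim and state that 53 evaluable per group gives about 74% exact power under 97% vs 99%, and that 59 gives about the same;
- if the normal-approximation figure of 82.5% is mentioned, label it as an approximation.

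Use the same score test in the final analysis, so that the stated error is the one the trial has.

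The cost is wording in the protocol and analysis plan, and a less favourable stated power. No patients are added and no clinical procedure changes. For comparison, 90% power with the Farrington-Manning test would need 87 evaluable per group, or 87 / 0.9 = 96.7, so 97 per group with 10% withdrawal.

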### Randomization

Treatment allocation occurs when the study participant meets the inclusion criteria and signs the informed consent form. All eligible patients will receive ATRA-ATO for induction therapy. Participants are randomized by permuted blocks to ensure there are similar numbers of participants in the intervention and control groups. The randomization allocation schedule is generated by a statistician with no other involvement in the study. Once consented, participants are allocated in a 1:1 ratio to the two arms of the study according to a computer-generated random sequence after achieving hematologic complete remission (HCR) (Figs. 1 and 2). Participants will be informed of their allocated treatment group following randomization.

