### Interventions

Patients with APL will be randomly assigned by a computer-generated, random-allocation schedule to one of two groups: the ATRA-RIF group (experimental group); the ATRA-ATO group (control group); patients with APL will be classified into three risk categories on the basis of WBC count and platelet count. Low risk is a WBC count < 10 × 10^9^/L and a platelet count ≥40 × 10^9^/L; intermediate risk is a WBC count < 10 × 10^9^/L and a platelet count < 40 × 10^9^/L; high risk is a WBC count ≥ 10 × 10^9^/L (Fig. 3).

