#### Relapse is defined as follow [12]:

Hematologic relapse is defined by bone marrow blasts of 5%, reappearance of blasts in the blood, or development of extramedullary disease. Molecular relapse: if studied pre-treatment it is defined by recurrence of minimal residual disease (MRD) as assessed by quantitative RT-qPCR or by multi-color flow cytometry.

The secondary outcomes of this trial are hospitalization days and medical costs in the two arms. The medical costs will be calculated for each patient. The hospitalization costs for induction and consolidation therapy will be calculated for inpatients. The hospital costs for induction therapy and consolidation therapy will be calculated for outpatients. All medical costs can be collected and multiplied by the unit cost of each resource use. After the patient is discharged from the hospital, we can obtain the medical costs from the medical record in hospital according to the patient’s name/case number. For the outpatients, the medical costs can be obtained from the outpatient system after the patient’s visit. Hospitalization days will be recorded over a 10-month time frame.

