### Data collection and management

Patient information will be entered into the paper case report forms (CRFs) promptly and synchronously with input into the electronic CRF. The occurrence of unexpected problems during this process should be recorded, and will be informed in a timely manner.

In order to ascertain the two randomized groups are similar, the demographic/disease characteristics including sex, age, region, body mass index (BMI) and medical history will be collected.

The committee that was responsible for the study design and the implementation process will ensure the effectiveness and integrity of the trial design. The committee will supervise the integrity and accuracy of data collection to control its quality. The committee also needs to evaluate key outcomes based on the clinical expertise of its members.

Data sharing is not applicable to this protocol article as no datasets have as yet been generated or analyzed during the current study. The results should be made public within 24 months of reaching the end of the study. The end of the study is the time point at which the last data items are to be reported, or after the outcomes of data are sufficiently mature for analysis as defined in the statistical analysis section. A full report of the outcomes should be made public no later than 3 years after the end of the study. Results will also be available through the Clinical Trials Registry.

Missing data will be reviewed to identify potential patterns, and examined to assess how these patterns impact our results. There are three types of missing data that can occur when the data are being collected [13]. When data are missing (completely) at random, unbiased results can still be obtained using the maximum likelihood method that will be used in the linear mixed model analysis. When data are not missing at random, we will analyze sensitivity using pattern mixture models and the results will be used to assess the impact of missing data on the reported conclusions.

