### Statistical analysis

Statistical analysis will be performed using SPSS software 11.0. The primary analysis will be conducted on the intention-to-treat principle. Descriptive analysis (calculations of averages, frequencies, proportions, or rates) will be conducted. Comparisons will be made using Student’s *t* test or the Mann–Whitney *U* test for comparison of continuous variables and Pearson’s *χ*^2^ test for dichotomous variables. Student’s *t* test will be used to compare variables of normal distribution. The Mann–Whitney *U* test will be used to compare variables of non-normal distribution. The chi-square test or Fisher’s exact test will be used for comparison of categorical variables between the two groups. Survival functions will be estimated using the Kaplan-Meier method and will be compared using the log-rank test. The medical costs will be retrospectively calculated for the patients involved in a prospective randomized controlled trial and will be compared in a post hoc analysis of the two groups. The Wilcoxon matched pairs test will be used to compare the medical costs between the RIF and ATO groups. All statistical tests will be two-sided, and the level of significance will be set at 0.05, except for the non-inferiority hypothesis.

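### The planned comparisons of hospital days and costs use neither hospital nor risk group, both known before randomization, and so give up some precision

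*Protocol article*

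**What the plan says.** The Eligibility criteria section names two sites: "Patients will be enrolled from the following hospitals: The First Affiliated Hospital of Xi’an Jiaotong University and Tang-Du Fourth Military Medical University of Chinese PLA". Under Interventions, "patients with APL will be classified into three risk categories on the basis of WBC count and platelet count". The inclusion limit on white cell count removes the high-risk category. That leaves low and intermediate risk, separated by a platelet count of 40 × 10^9/L.

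On timing, the Randomization section states that "participants are allocated in a 1:1 ratio to the two arms of the study according to a computer-generated random sequence after achieving hematologic complete remission". On method it states: "Participants are randomized by permuted blocks to ensure there are similar numbers of participants in the intervention and control groups". It mentions no strata, either to include or to exclude them.

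The outcomes at issue are given with the outcome definitions: "The secondary outcomes of this trial are hospitalization days and medical costs in the two arms". Costs cover induction and consolidation. They are taken from the hospital record for inpatients and from the outpatient system for the rest.

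The Statistical analysis section assigns continuous variables, and so hospital days, to a t test or a Mann–Whitney test. For costs: "The Wilcoxon matched pairs test will be used to compare the medical costs between the RIF and ATO groups". Neither hospital nor risk group appears in these tests. The Data collection and management section says, for checking that the arms are similar, that "the demographic/disease characteristics including sex, age, region, body mass index (BMI) and medical history will be collected"; hospital and risk group are not among the examples. The same section mentions a linear mixed model in connection with missing data, but gives no outcome or covariates for it, and the Statistical analysis section does not mention it.

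**The concern.** Days in hospital and money spent can plausibly depend on where a patient is treated, through local discharge practice and local charges. They may also depend on how ill the patient was at presentation. Part of the cost total arises during induction, when every patient receives the same regimen. Variation in that part says nothing about the consolidation arms and adds only noise to the comparison.

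The trial will hold both factors for every patient. A test that ignores them leaves any variation they explain in the error term. At stake is the width of the interval around the differences in days and in costs, the two results meant to show the practical advantage of the oral formula. The primary non-inferiority conclusion is not affected.

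**Working it through.** **1. Are both factors known before randomization?** Yes. Hospital is known at enrolment. Risk group rests on white cell and platelet counts. Intermediate risk needs platelets below 40 × 10^9/L, whereas remission needs more than 100 × 10^9/L, so the classification must use counts taken before remission, and allocation follows remission.

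**2. Do the stated tests use them?** No. The t test, the Mann–Whitney test and the matched-pairs Wilcoxon test, as described, have no hospital or risk term.

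**3. The plan's own figure.** There is none for days or costs; the sample size is set for disease-free survival only. This check takes from it just the arm size: 53 / 0.90 = 58.9, so 59 per arm and 118 in total, as stated.

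**4. Precision.** For a difference in means, adjusting for baseline factors that explain a share R² of the variance multiplies the standard error by √(1 − R²). The document gives no standard deviation, hospital shares or between-hospital difference, so R² is assumed. The power column takes an effect that has 80% power unadjusted (two-sided 0.05, 59 per arm): power = Φ[(1.960 + 0.842)/√(1 − R²) − 1.960].

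| R² (assumed) | SE multiplier | Fall in SE | Power |
|---|---|---|---|
| 0.05 | 0.975 | 2.5% | 82% |
| 0.10 | 0.949 | 5.1% | 84% |
| 0.20 | 0.894 | 10.6% | 88% |
| 0.30 | 0.837 | 16.3% | 92% |

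**5. Check by simulation.** Inputs: 118 patients, blocks of 4 across the whole trial, two equal-sized hospitals, within-hospital SD of 1, 3,000 repeats. With hospitals 1 SD apart (R² = 0.20), the SD of the estimated arm difference was 0.204 unadjusted and 0.185 adjusted, a ratio of 0.91. With hospitals 0.5 SD apart (R² = 0.059), it was 0.189 and 0.182, a ratio of 0.96. Both are close to the formula.

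**6. Does the point depend on how the blocks were built?** No. With blocks stratified by hospital (equal hospitals, 1 SD apart), the unadjusted estimate had a true SD of 0.186. An ordinary t test would still report about √(1.25 × 2/59) = 0.206, because the within-arm variance of 1 + 0.25 × 1² = 1.25 includes the hospital difference. Under either form of allocation, the analysis needs hospital in it to realise the precision.

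**7. Could imbalance reverse the hospital-day result?** If the arms differed by 10 to 15 percentage points in hospital mix and the hospitals differed by 5 days (both assumed), the arm difference would move by 0.10 × 5 = 0.5 to 0.15 × 5 = 0.75 day. The Discussion expects patients on the oral formula to be treated at home and those on intravenous arsenic in hospital during remission therapy, so the contrast should be far larger than that.

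**8. Why not adjust disease-free survival?** Expected failures are 59 × 0.03 + 59 × 0.01 = 1.77 + 0.59 ≈ 2.4 in total, too few to support covariates.

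**The case against.** The strongest reply is that unadjusted two-sample comparisons in a randomized trial are valid, that covariates for secondary outcomes are commonly left to a statistical analysis plan, and that the article claims no power for days or costs. Validity stands: nothing here is biased. The appeal to an unseen plan carries less weight, because the article does not stay silent. It names the tests, and they have no place for either factor. The linear mixed model mentioned for missing data does not fill the gap, since neither its outcome nor its covariates are given.

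A second reply is that the benefit is assumed. That also stands. At 5% of variance explained the gain is slight, the link between risk group and days or costs is not shown in the document, and √(1 − R²) describes a difference in means, not the gain over a rank test.

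A reader might go further and infer that allocation ignores hospital and risk group, so that the blocks should be changed. The document does not support this. It gives the method and its aim but never says that the list is unstratified or shared between hospitals, and a journal article commonly leaves such detail to the full protocol. Changing lists part-way through an open-label trial that began recruiting in July 2016 is also not clearly cheap. A reader might equally infer that chance imbalance biases the comparison. It does not, because the unadjusted standard error already allows for it.

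**Conclusion.** The point holds as a modest one about analysis. The stated tests for hospital days and costs leave out two factors that are known before randomization and could be used at almost no cost. The consequence is lost precision only. Its size is not computable from the document; under an assumed 5% to 30% of variance explained, the standard error would be about 2.5% to 16% smaller with adjustment. The hospital-day conclusion is unlikely to reverse; the benefit is a sharper estimate, probably more useful for costs. No fault in the allocation is established.

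**What to change.** In the Statistical analysis section, replace the tests for hospital days and costs with a prespecified independent-groups analysis that includes hospital and risk group (low or intermediate). One suitable form is a regression giving the arm difference in mean days and mean cost, with robust or bootstrap standard errors because costs may be skewed. A rank test stratified by hospital can serve as a sensitivity analysis. The matched-pairs cost test needs replacing in any case, since the arms are independent and no matching is defined; that is a separate matter, but one rewrite can settle both.

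Settle the model before the outcome data are examined. The Blinding section says that the analyst is unblinded and takes part in data collection, and the cost comparison is described as post hoc, so covariates chosen later would be open to question. Keep the disease-free survival analysis unadjusted, and leave the allocation procedure as it is.

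The cost is a few lines of text, slightly more analysis work, and a model where a simple test stood. Both factors come from information the trial already holds.
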